### Procedure

Treatment coordinators of the institute and the school psychologists will screen youth for inclusion and exclusion criteria. After that, parents or legal representatives will receive an information letter containing a digital link and response letter to sign-up if they wish their child to participate in the study (active informed consent). In addition, adolescents will be informed approximately a week before the first screening by two research assistants in their classroom or group. If potential participants are absent or if they need extra information, information will be given individually. If adolescents also agree with participation, active written informed consent will be obtained. After that, participants will be randomly allocated to either intervention group or control group. Randomization will take place at individual level using a stratified block design to ensure equality between conditions. The stratified block randomization will be based on three factors: gender, age, and IQ. Parents, mentors, and teachers will be informed by a letter about the condition their child is assigned to.

Before filling out the pre-test, all participants will complete a short questionnaire containing questions regarding their living group or class and additional therapies (i.e., physiotherapy, speech therapy, social skills training). After that, the pre-test (T0) will be assessed. After the pre-test, youth in the intervention group will participate in the intervention “The Growth Factory” with six sessions lasting 25 to 40 min. Moreover, participants will receive care as usual parallel with “The Growth Factory”. Parents will also receive a login to be able to follow the sessions at home. Youth in the control group will receive care as usual. After completion of the trial participants in the control group will be given the opportunity to participate in “The Growth Factory”.

After completing the sessions of “The Growth Factory”, all participants will be assessed at post-test (T1) and a follow-up at 3 months (T2) and 6 months (T3). Furthermore, participants in the intervention group will also receive a booster session directly after the 3 months follow-up. Research assistants will guide the participants individually during the assessments and intervention in a silent room using a protocol. In line with the assessment protocol all questions will be read aloud and a standardized clarification for questions will be used. Additionally, assistance will be provided in case participants need help to complete the forms. To minimize any connection between the intervention and the measures, different research assistants will collect the measures apart from the one who guided the youth during the sessions. All research assistants will participate in four training sessions and have a bachelor or master degree or are in the final year obtaining their degree.

During the sessions, participants in the intervention group will receive a small gift (i.e., a refrigerator magnet with the five steps to ask for help in an appropriate way, and a bracelet with the ‘recipe of growth’) after completing session five and six. Furthermore, all participants receive a thumbs-up flashlight and small ‘brain stressball’ after completing the first and second follow-up measurement.

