### Participants

Participants that will be selected for the study are (late) adolescents (12 to 23 years) with mild to borderline intellectual disabilities, including youth with mild intellectual disabilities (IQ 50–69) and borderline intellectual functioning (IQ 70–85) and deficits in adaptive functioning. Besides an intellectual disability participants could have accompanying physical disabilities or psychiatric problems. Participants are clients in residential care or students in special education. Exclusion criteria are the presence of severe emotional problems hindering participation in the study, such as extreme aggression problems or an acute unstable mental condition. Participants who agree to participate will be included in the study when both adolescent and parents or legal representative provide written informed consent.

A power analysis [50] was performed to calculate the sample size required in the present study. Based on previous research on the effectiveness of mindset interventions in education [39], the expectation is to find a small to medium effect (*d* = 0.25). The power calculation (two-tailed, alpha 0.05, statistic power 0.80) based on a three measurements design shows that 106 participants are necessary. Therefore, our aim is to include *N* = 120 participants (*n* = 60 intervention group; *n* = 60 control group) in the RCT taking into consideration 10% attrition.

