### Care as usual

Participants assigned to the control condition will receive care as usual. Adolescents recruited from a special education school attend the school curriculum and are supervised by a mentor teacher. In addition, a school psychologist is involved in the educational learning process and provides specific orthopedagogical advise. Each student receives a ‘developmental perspective plan’ based on the youth’s specific developmental needs. Furthermore, additional therapies are offered depending on the youth’s care need, such as resilience training and creative arts therapies (e.g., art, music, and/or dramatherapy). Specifically, for youth with physical disabilities physiotherapy, ergotherapy, and medical assistance are offered. Adolescents recruited from a specialized residential care institute receive an ‘individual treatment plan’ in which treatment goals and plans are formulated based on the youth’s specific developmental needs. A multidisciplinary team is involved in these treatment programs. One of the group care workers is the youth’s mentor who provides guidance and support based on the treatment goals and plans. Furthermore, additional therapies are offered, such as physiotherapy, medication management, and resilience training; and sometimes a family social worker is involved. Also, in residential care youth receive medical assistance when needed. Youth care workers provide care using a “strength based approach” which focusses on the individuals’ strengths, potential, and self-determination.

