### Screening measures

For all participants, information regarding gender, age, IQ scores, and diagnosis will be provided by the treatment coordinator or school psychologist. Participants will provide information about setting (residential care group or homestay) and attributional treatment (e.g., physiotherapy, speech therapy, social skills training).

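### Setting (special education or residential care) is known before allocation but reaches the models only through a baseline test; fixing it as a prespecified covariate is a free, minor improvement

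*Protocol article*

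**What the plan says.** On allocation, the Procedure section states: "Randomization will take place at individual level using a stratified block design to ensure equality between conditions". It then names the factors: "The stratified block randomization will be based on three factors: gender, age, and IQ".

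On setting, the Participants section states: "Participants are clients in residential care or students in special education". Screening is done by the institute's treatment coordinators and the school psychologists, so the recruiting setting is known before allocation.

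The Care as usual section describes the two settings separately. For schools: "Adolescents recruited from a special education school attend the school curriculum and are supervised by a mentor teacher". For residential care: "Adolescents recruited from a specialized residential care institute receive an ‘individual treatment plan", and "A multidisciplinary team is involved in these treatment programs". The intervention arm keeps this background care: "Moreover, participants will receive care as usual parallel with" the programme (Procedure).

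The footnote to Table 1 allows the mentor to be either a school mentor or a social worker from the group. Under Secondary outcome measures, the treatment-motivation items were reworded because youth in institutional care already receive counselling, and two items are answered only by those who get extra counselling.

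Under Statistical analyses, background variables are compared at baseline with t-tests, and those that differ become covariates in all effectiveness models. Age and gender are the examples given. Setting is not named there or among the moderators. Under Screening measures, the youth report whether they live in a residential group or at home.

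**The concern.** The article itself gives reasons to expect setting to matter for how outcomes develop, not only for their starting level: the care differs in kind, and so do the rater of the mentor outcomes and the applicability of some treatment-motivation items. A variable of this sort, known before allocation, is normally placed in the model in advance.

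Here its inclusion depends on a significance test at baseline. Such a test reacts only to large imbalances and takes no account of how strongly the variable predicts the outcome. A moderate imbalance on a prognostic variable would be left in the estimate, and whether setting is in the model would be decided after looking at the data. At stake are a little precision and the clarity of the prespecified analysis.

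**Working it through.** **Inputs from the article (Participants):** 60 per arm, d = 0.25, two-tailed alpha 0.05, power 0.80, three measurements, 106 participants before 10% attrition.

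**Assumptions, not in the article:** correlation between measurements 0.5; setting mix 50:50 (20:80 and 30:70 also shown); threshold 0.05 for the baseline test; setting unrelated to gender, age and IQ; setting effect 0.5 SD on the analysed contrast (0.2 and 0.8 also shown).

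**1. The plan's own figure.** For the group-by-time interaction, f = d/2 = 0.125 and lambda = f² × N × m / (1 − rho) = 0.015625 × 106 × 3 / 0.5 = 9.94, with 2 and 208 degrees of freedom. Power is 0.807 and 106 is reproduced. Then 106/0.9 = 117.8, so 118, which 120 covers. A plain comparison of two means at d = 0.25 needs 252 per arm and does not reproduce 106. The sample size therefore fits a test of difference in change.

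**2. What can shift that test.** A setting difference that is the same at every measurement cancels. Only a difference between settings in change over time remains. If that difference is g (in SD of the analysed contrast) and the arms differ by D in the share from one setting, the shift in the estimate is D × g.

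**3. Distribution of D.** With 60 of 120 participants in each setting and 60:60 allocation, the number k from one setting in one arm is hypergeometric. Var(k) = 60 × 0.5 × 0.5 × 60/119 = 7.56. D = (2k − 60)/60, so SD(D) = 2 × 2.75/60 = 0.092. The corresponding values are 0.084 at 30:70 and 0.073 at 20:80.

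**4. When the baseline t-test fires (50:50 mix).**

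| Split between arms | Imbalance (points) | t-test p | Probability of at least this |
|---|---|---|---|
| 33 v 27 | 10.0 | 0.277 | 0.361 |
| 34 v 26 | 13.3 | 0.147 | 0.201 |
| 35 v 25 | 16.7 | 0.069 | 0.100 |
| 36 v 24 | 20.0 | 0.029 | 0.044 |

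The rule acts in 4.4% of randomisations. Imbalances of 10 to 16.7 points occur in 0.361 − 0.044 = 0.317 and are left unadjusted. At 30:70 the rule first acts at 16.7 points (p = 0.047, probability 0.072), leaving 0.319 − 0.072 = 0.247 with an unadjusted imbalance of 10 points or more. At 20:80 it also first acts at 16.7 points (p = 0.022, probability 0.039), leaving 0.254 − 0.039 = 0.215.

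**5. Size of a single shift.** At 16.7 points and g = 0.5, the shift is 0.167 × 0.5 = 0.083 SD, one third of d = 0.25. Over repeated randomisations the shift averages zero.

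**6. Cost in precision (50:50 mix, unit residual SD).**
- Unadjusted, g = 0.5: SE = √(2/60 + (0.5 × 0.0917)²) = √(0.03333 + 0.00210) = 0.188.
- Setting in the model: SE ≈ √(2/60) × √(1 + 1/119) = 0.183.
- Unadjusted, g = 0.2: √(0.03333 + 0.00034) = 0.183, so no visible gain.
- Unadjusted, g = 0.8: √(0.03333 + 0.00538) = 0.197.

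**7. Simulation check.** With g = 0.5 and 40,000 trials, the SE was 0.188 unadjusted, 0.187 under the test-triggered rule and 0.183 with setting always included. Type I error was 0.050, 0.049 and 0.051 respectively. In a separate run of 10,000 trials with an illustrative treatment effect of 0.5 SD, power was 0.753 unstratified and unadjusted, 0.776 unstratified and adjusted, and 0.774 stratified and adjusted.

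**The case against.** The strongest case on the other side has four parts.

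- **Nothing is contradicted.** The article never claims that setting is balanced. Leaving out a fourth factor at N = 120 is defensible: with two levels per factor there would be 16 strata of 7 to 8 participants, and incomplete blocks could weaken balance on the chosen factors. This stands.
- **The two kinds of usual care do not separate the arms.** A reader might infer that the trial has two different control conditions that confound the comparison. The documents do not support this: allocation is individual, and intervention participants also receive the usual care of their own setting.
- **The harm is small.** A reader might infer a biased result. The error has mean zero and is already reflected in the standard error, and constant setting or rater differences cancel in change over time. The mentor report supplements a self-reported primary outcome, and mentors rate only three measures. All of this stands.
- **A covariate route exists, and an article need not list every covariate.** This stands only in part. The examples in the covariate rule are not exhaustive, and a setting item is recorded. But the article does state the rule, and step 4 shows that it would seldom admit setting. The recorded item also asks about living situation, which need not equal recruitment setting.

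**Conclusion.** The point holds as a minor one. Setting is known before allocation and plausibly affects the course of outcomes, yet the stated rule would adjust for it in about 4% of randomisations (4% to 7% over the mixes examined) and would leave imbalances of 10 points or more unadjusted in about 22% to 32%. The consequence is a small loss of precision: about 2.6% of the standard error at an assumed 0.5 SD setting effect, nil at 0.2 SD, and about 7% at 0.8 SD. The setting mix, the setting effect and the test threshold are all assumptions.

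The figures do not show that the randomisation is faulty or that stratifying on setting is needed. Adjustment alone recovers what stratification would give. Nor does the secondary aim of learning for whom the programme works oblige the plan to add another interaction at this sample size.

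**What to change.** In Statistical analyses, state that recruitment setting (special education or residential care) is a prespecified covariate in every effectiveness model, with its interaction with time, whatever the baseline tests show. The interaction is needed because in a repeated-measures model a main effect of setting alone leaves the group-by-time contrast unchanged. Take the variable from site records rather than from the youth's report of living situation. The article does not say that the two groups are mutually exclusive, so define setting by the site through which the participant was recruited.

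The cost is a sentence or two of analysis text and one more model term with its time interaction. No extra participants or data collection are needed, and the randomisation list is untouched. Setting as a fourth stratification factor or as a further moderator is optional.

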### Instruments/measures

Instruments will be adjusted to reduce the complexity of the questionnaires for the participants with intellectual disabilities using the Dutch guideline for the development and adjustment of diagnostic instruments for people with intellectual disabilities [55]. The answering categories of the different questionnaires will be unified into one format of answering catergories ranging from ‘completelyuntrue’ to ‘completely true’, and coloured emoticons corresponding with the answering categories will be added. Difficult words and sentences will be simplified or slightly rephrased to avoid misunderstandings due to literal interpretation. The pilot studies showed the questionnaires to be suitable for youth with intellectual disabilities [46]. Table 1 shows an overview of study outcome measures and the informants that will be involved in each assessment.

**Table 1 Tab1:** Overview of assessments

	T0	Session 1–6	T1	T2	T3
Adolescent					
Mindset (MQ)	x		x	x	x
Empowerment (EMPO Youth 2.0)	x		x	x	x
Behavior problems (BPM-Y)	x		x	x	x
Self-esteem (RSES)	x		x	x	x
Treatment motivation (MYTS)	x		x	x	x
Therapeutic alliance (TASC-r)	x		x	x	x
Challenge seeking (Puzzles)	x		x	x	x
Impact of social exclusion (Cyberball game)	x		x	x	x
Intervention satisfaction (SRS)		x			
Mentor^a^					
Mindset (MQ)	x			x	x
Empowerment (EMPO Youth 2.0)	x			x	x
Behavior problems (BPM-P)	x			x	x

^a^Mentor is defined as school mentor or social worker from the group

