### Statistical analyses

Following the intention-to-treat principle, the data from all participants randomized to either the intervention or control group will be analysed. Multiple imputations will be used for missing values at post-intervention and follow-up measurements. In addition, a completers only analysis will be conducted (i.e., participants that completed five or six sessions). The results will be reported in accordance with the CONSORT Statement [49].

Possible baseline differences between the two groups in background variables (e.g., age, gender) and relevant study variables will be examined using independent-sample t-tests. In case of differences at baseline, variables will be included as covariates in all models testing the effectiveness of the intervention. Furthermore, the effectiveness of the intervention will be analysed using repeated measures ANOVA for differences within subjects (i.e., pre-test, post-test, follow-up 1, and follow-up 2 measurements) and between subjects (intervention versus control group). In addition, intervention satisfaction, level of intellectual disability, age, baseline mindset, and gender will be tested as moderators of the effects of the online mindset intervention.

These moderator effects will be tested using three-way interactions in our repeated measures design. The effect of the mindset intervention on the secondary outcomes measures, (i.e., empowerment, internalizing problems, attention problems, externalizing problems, and total behavior problems, self-esteem, treatment motivation, therapeutic alliance, challenge seeking, and impact of social exclusion) might be mediated by mindset. This will be tested in several mediation analyses in Mplus [68].

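### The procedure describes random allocation, and an undated letter disclosing it to the mentors who rate outcomes, before the pre-test (T0), so the baseline is not protected from knowledge of the arm

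*Protocol article*

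**What the plan says.** The Procedure section runs in time order. Once parents and adolescent have consented, "After that, participants will be randomly allocated to either intervention group or control group". The stratification is then given: "The stratified block randomization will be based on three factors: gender, age, and IQ". That paragraph closes with the disclosure: "Parents, mentors, and teachers will be informed by a letter about the condition their child is assigned to".

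The next paragraph opens with "Before filling out the pre-test, all participants will complete a short questionnaire containing questions regarding their living group or class and additional therapies", continues with "After that, the pre-test (T0) will be assessed", and then gives the start of treatment: "After the pre-test, youth in the intervention group will participate in the intervention".

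Table 1 (Instruments/measures) lists mentor ratings of the MQ, EMPO Youth 2.0 and BPM-P at T0, T2 and T3. Its footnote reads "Mentor is defined as school mentor or social worker from the group". The Primary outcome measure section makes the adolescent's own MQ the main instrument, with the mentor's MQ in addition. Under Screening measures, gender, age and IQ come from the treatment coordinator or school psychologist.

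Statistical analyses treats the pre-test as one of four levels of the within-subject factor in a repeated measures ANOVA and tests baseline mindset as a moderator. A variable that differs between arms at baseline on a t-test becomes a covariate.

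**The concern.** A baseline is safe to use as a reference because allocation cannot have influenced it. That guarantee lapses once the arm is assigned, and especially once it is known, before the measurement is taken. A mentor told that a pupil is about to receive the programme, or is not, may rate that pupil differently. An adolescent who hears the arm from a parent or teacher may answer differently.

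T0 matters in two ways here. It anchors every group-by-time contrast, and baseline mindset is itself tested as a moderator. A T0 shift caused by disclosure could look like an intervention effect or hide a real one.

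The planned remedy, a baseline t-test followed by covariate adjustment, does not repair this. It would adjust for a variable that allocation may already have affected. It would also usually miss the problem: a true 0.2 SD shift is significant on a two-sample t-test with 54 per arm only about 18% of the time.

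**Working it through.** **1. Order of events.** Consent, then allocation, is explicit. T0 comes later in the same narrative, after a short questionnaire, and sessions follow T0. Nothing in the text places T0 before allocation. The letter is described between allocation and T0 but carries no date, and the flow diagram (Fig. 1) is not available in the text reviewed.

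**2. Who knows and who rates.** Letter recipients: parents, mentors, teachers. T0 raters: adolescents and mentors. The overlap in the text is the mentors. Adolescents are not named as recipients, but no concealment from them is described either. The Procedure section separates the assistants who collect measures from those who guide sessions; it does not say that assessors are unaware of the arm.

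**3. Does randomisation need T0 data?** No. Gender, age and IQ all come from staff, so T0 can be completed first.

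**4. The plan's own sample size.** Inputs from the Participants section: d = 0.25 (so f = 0.125), alpha 0.05, power 0.80, three measurements. Assumed correlation between waves r = 0.5, which the document does not give. For the group-by-time test with m waves and total N, λ = N·m·f²/(1 − r), with df m − 1 and (N − 2)(m − 1).
- N = 106: λ = 106 × 3 × 0.015625 / 0.5 = 9.94, df 2 and 208, power 0.807. The stated 106 is reproduced.
- Attrition: 106 / 0.90 = 117.8, so 118; the planned 120 covers it.

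The sample size is not in dispute. The result supports r = 0.5 as a reasonable working value.

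**5. Illustration of a T0 shift.** Assumptions: compound symmetry, SD 1, r = 0.5, no true effect, n = 60 × 0.9 = 54 per arm. Let δₜ be the between-arm difference at wave t and δ̄ its mean over waves. Then λ = (n/2) × Σ(δₜ − δ̄)² / (1 − r), with df m − 1 and (2n − 2)(m − 1).

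| Scenario | δₜ | Σ(δₜ − δ̄)² | λ | df | False positives |
|---|---|---|---|---|---|
| Four waves, 0.2 SD at T0 only | 0.2, 0, 0, 0 | 0.0300 | 27 × 0.0300 / 0.5 = 1.62 | 3, 318 | 16.1% |
| Four waves, 0.1 SD at T0 only | 0.1, 0, 0, 0 | 0.0075 | 0.405 | 3, 318 | 7.5% |
| Four waves, 0.2 SD, half persists | 0.2, 0.1, 0.1, 0.1 | 0.0075 | 0.405 | 3, 318 | 7.5% |
| Four waves, 0.2 SD, all persists | 0.2, 0.2, 0.2, 0.2 | 0 | 0 | 3, 318 | 5.0% |
| Mentors' three waves, 0.2 SD at T0 only | 0.2, 0, 0 | 0.0267 | 1.44 | 2, 212 | 17.1% |
| Mentors' three waves, 0.2 SD, half persists | 0.2, 0.1, 0.1 | 0.0067 | 0.36 | 2, 212 | 7.8% |

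For the four-wave, T0-only shift of 0.2 SD, the rate is 12.6% at r = 0.3 and 24.7% at r = 0.7.

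The four-wave rows apply to self-report, where awareness at T0 is only possible. The three-wave rows apply to the mentor ratings, where the rater is told.

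**The case against.** The strongest reply is that the document never says the letter goes out before T0. The sentence has no time marker, it closes the paragraph on randomisation, and Fig. 1 might show a different order. This stands: the order of allocation and T0 is described, while the timing of disclosure is inferred from its position.

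A second reply is that the primary outcome is self-report and adolescents are not among the letter's recipients. This also stands. A reader might infer that the whole baseline is open; the text supports that concern directly only for mentor ratings.

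Third, informed raters stay informed. A reader might infer that any T0 shift passes in full into the difference in change. It does so only if it is confined to T0; a constant shift cancels in the group-by-time test, and partial persistence leaves much less, as the table shows. The size and direction of any shift are unknown.

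Fourth, a reader might infer that someone who withdraws between allocation and T0 cannot enter the intention-to-treat analysis, because the plan says "Multiple imputations will be used for missing values at post-intervention and follow-up measurements". That sentence does not exclude imputing a missing baseline. The same section promises to analyse all randomised participants, and handling of a missing T0 may be left to an analysis plan not shown here.

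Separating assessors from session guides gives some protection, but it is not blinding and does not cover the mentors' own ratings.

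What remains is that T0 is described after allocation without any stated reason or safeguard, and that raters who are told the arm contribute to it.

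**Conclusion.** The point holds in a limited form and should be fixed. As described, T0 follows random allocation, and the mentor baseline may be an unblinded, post-randomisation rating. For the self-reported primary outcome, awareness at T0 is possible but not stated.

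The harm depends on a shift that differs between T0 and later waves. Under the assumptions above, the illustrative false-positive rate runs from the nominal 5%, if a 0.2 SD shift persists fully, to about 16% over four waves (about 17% over the mentors' three) if it is confined to T0. These are scenarios, not estimates: neither the shift nor the correlation is in the document, and the bias could equally mask a real effect. The document does not show that bias will occur; it shows that an avoidable route to it has been left open.

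**What to change.** Reorder the Procedure section: consent, adolescent T0 and mentor T0, randomisation, allocation letter, session 1. If lists must be drawn up earlier for logistics, state that allocation stays concealed from participants, parents, mentors, teachers and T0 assessors until both T0 forms are in. If this is already the practice, correct the text and date the letter relative to T0.

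The change needs no new visit, measure or staff, and it does not affect the sample size. Its one cost is that sessions can be scheduled only after T0. It also avoids having randomised participants without a baseline.
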